### Statistical considerations

#### Power and sample size

To calculate sample size, a 3.5 ml/(kg min) difference of measurements in VO_2max_ was considered as a minimum effect to decrease the risk of cardiovascular disease [4, 5] with standard deviations for the intervention group and the control group of 2.6 and 4.6, respectively [14], assuming a 95 % confidence level, 5 % alpha error, and 20 % beta error, with a 1:1 ratio between groups. Using Epidat software (version 4.0), it was found that a sample of 20 individuals per group would be needed, plus an estimated 10 % for possible losses.

#### Analysis plan

All analyses will be conducted according to the intention-to-treat principle, using a normality test, homoscedasticity test, or linearity test as necessary, to verify assumptions for the use of parametric statistics. As long as all assumptions of normality are met, analysis of covariance (ANCOVA) [52] will be used to control for the baseline values and adjust for possible confounding variables. In this regard, means and standard deviations will be used as summary measures. In the event that the requirements for parametric analysis are not met, a Mann–Whitney U test will be adopted, and values will be reported in medians and interquartile ranges. A two-tailed significance test with a *P* < 0.05 and a 95 % confidence level will be used. To manage missing data, multiple imputation procedures will be used to replace missing values for the primarily variables of interest, following the guidelines set forth by Stern *et al.* [53]. Briefly, multiple imputation procedures create several sets of plausible imputed data, based on the Bayesian approach, and combine the results obtained with each one to create a value for each missing data point. Stata software (version 13) will be used to carry out all statistical procedures.

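### Preliminary assumption tests decide whether the primary result is a baseline-adjusted ANCOVA or an unadjusted Mann–Whitney test; the trigger is ambiguous and the switch gains nothing for unequal variance

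*Protocol article*

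**What the plan says.** The Analysis plan section of the protocol article sets a two-step rule. Assumptions are checked first, "using a normality test, homoscedasticity test, or linearity test as necessary, to verify assumptions for the use of parametric statistics". ANCOVA, chosen there to control for baseline and for possible confounders, is used if the assumptions hold. Otherwise: "In the event that the requirements for parametric analysis are not met, a Mann–Whitney U test will be adopted". The fallback is summarised by group medians and interquartile ranges. No covariate and no between-group estimate is attached to it, and the text does not say whether final values or changes are ranked.

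The two halves of the rule describe the trigger differently. The sentence that permits ANCOVA speaks only of normality. The sentence that invokes the fallback speaks of the requirements for parametric analysis, and the list before both includes homoscedasticity and linearity.

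The Power and sample size section targets 3.5 ml/(kg min), a "difference of measurements in VO_2max_ was considered as a minimum effect to decrease the risk of cardiovascular disease", "with standard deviations for the intervention group and the control group of 2.6 and 4.6, respectively", and finds that "a sample of 20 individuals per group would be needed". It does not say whether these are SDs of final values or of change.

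**The concern.** A test-then-switch rule lets a noisy preliminary test settle what the trial reports as its main finding. On one branch the reader gets a baseline-adjusted mean difference in ml/(kg min), which can be compared directly with the 3.5 used to size the trial. On the other branch the reader gets a rank-test P value and two medians, without the adjustment that the plan set out to make.

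The sample size calculation itself uses clearly unequal SDs. If equality of variance is one of the conditions, the planning figures point to a substantial chance of landing on the second branch. Unequal spread is also a poor reason to go there: Mann–Whitney is not a clean test of location when spreads differ, while ANCOVA with equal arms tolerates unequal variance well. At stake are the estimand, precision and the reported effect measure of the primary outcome.

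**Working it through.** **Inputs from the protocol.** Difference 3.5; SDs 2.6 and 4.6; two-sided alpha 0.05; power 0.80; 1:1 allocation; 20 per group, 22 after the 10% allowance. **Assumed, not in the protocol:** normal data; baseline–final correlation r from 0 to 0.8; pre-tests at the 5% level.

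**1. The plan's own figure.** Normal approximation: n = (1.960 + 0.842)² × (2.6² + 4.6²) / 3.5² = 7.849 × 27.92 / 12.25 = 17.9, so 18 per group. With the unequal-variance (Welch) t test, power is 0.796 at 19 and 0.818 at 20 per group, which gives 20. The stated sample size is reproduced and is not in question. It is a calculation for an unadjusted comparison.

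**2. How often a variance test rejects.** Variance ratio = (4.6/2.6)² = 21.16/6.76 = 3.13. The upper 2.5% point of F with 19 and 19 df is 2.526, so the power of the two-sided F test is P(F > 2.526/3.13) = P(F > 0.807) = 0.677. At 22 per group it is P(F > 2.409/3.13) = 0.723.

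**3. How often the gate fires.** Simulation, 20 per arm, planning SDs read as final-value SDs, tests on ANCOVA residuals, r equal in both arms:

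| Gate | r = 0 to 0.5 | r = 0.7 to 0.8 |
|---|---|---|
| Levene or Shapiro–Wilk | 0.60–0.62 | 0.52–0.55 |
| Brown–Forsythe or Shapiro–Wilk | 0.55–0.56 | 0.45–0.50 |
| Bartlett or Shapiro–Wilk | 0.66 | 0.55–0.61 |

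A common regression slope in both arms, instead of a common correlation, gives 0.56–0.96. With equal SDs the gate fires in about 0.10. If only normality is tested, it fires in about 0.10 under the planning SDs with equal correlation, and in 0.19–0.31 with a common slope and high correlation.

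**4. Power at a true difference of 3.5, 20 per arm, final-value SDs, equal r.**

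| r | ANCOVA | Mann–Whitney, final values | Loss (points) |
|---|---|---|---|
| 0 | 0.82 | 0.80 | 2 |
| 0.3 | 0.84 | 0.79 | 5 |
| 0.5 | 0.90 | 0.80 | 10 |
| 0.7 | 0.97 | 0.79 | 18 |

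The full procedure with a Levene-or-Shapiro–Wilk gate has power 0.84 at r = 0.5 and 0.87 at r = 0.7, which is 6 and 10 points below ANCOVA. A separate run gave 91% against 84% and 98% against 86%, or 7 and 12 points. With a normality-only gate, power is 0.83/0.85/0.90/0.95 at r = 0/0.3/0.5/0.7, a loss of at most about 2 points.

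**5. If 2.6 and 4.6 are SDs of change** (baseline SD of 4.0 assumed): ANCOVA 0.81, Mann–Whitney on change 0.80, Mann–Whitney on final values 0.48. The loss is near nil or large, depending on a scale that the plan does not fix.

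**6. Type I error under the planning SDs.** ANCOVA 0.051–0.052 at r = 0.5 and 0.7; gated procedure 0.053–0.054.

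**The case against.** The strongest reply is that the gate may not include homoscedasticity at all. ANCOVA is permitted on a condition about normality, and the homoscedasticity test sits in a list joined by *or* and qualified by *as necessary*. On that reading the switch is uncommon and costs almost nothing. This stands as a real alternative reading. It does not remove the point, because the fallback sentence uses the broader condition and the two need reconciling.

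A reader might infer from the unequal planning SDs that the protocol itself expects ANCOVA's conditions to fail, so that the rank test is the likelier primary analysis. The documents do not support that without qualification. The SDs are sample-size inputs taken from one cited study, the scale is not stated, and ANCOVA's assumption concerns residual variance. Even with homoscedasticity in the gate, a Brown–Forsythe version at high correlation fires in only 45–50% of trials.

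A reader might also infer an underpowered trial or an invalid test. Neither follows. Mann–Whitney on final values keeps about the planned 80% when the SDs are final-value SDs, so what is lost there is power above the design level. Type I error is not materially inflated.

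It is fair, too, that test names, levels and an accompanying effect estimate are often left to an analysis plan that is not shown. The switching rule and the unadjusted fallback, however, are fixed in this text. Nor does the use of multiple imputation in the same paragraph rule out a rank test, since rank statistics can be pooled approximately across imputed sets.

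**Conclusion.** The point holds in a conditional form. Followed as written, the rule can replace a baseline-adjusted difference with an unadjusted rank comparison on the strength of a preliminary test, and it gains nothing where the failed assumption is equal variance.

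Its size depends on three things the text leaves open:

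- **The trigger.** With homoscedasticity included, the switch rate is roughly 45–65% for common tests with equal correlation in the arms. With normality alone it is about 10%.
- **The correlation.** Mann–Whitney on final values loses 2–5 power points against ANCOVA at r = 0–0.3, about 10 at 0.5 and about 18 at 0.7. The gated procedure loses about 6–12 at r = 0.5–0.7.
- **The scale.** The loss is near nil if the SDs describe change and change is ranked.

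The harm is to the estimand, precision and reporting of the primary result. The sample size is sound. Severity: should-fix.

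**What to change.** Replace the switching rule with one primary analysis: ANCOVA of final VO2max on group and baseline VO2max, keeping any prespecified covariates, applied whatever the diagnostic tests show and reported as the adjusted mean difference with its 95% CI. Keep the assumption checks as diagnostics only. Make Mann–Whitney, or another rank-based method, a sensitivity analysis, and state whether it ranks final values or changes. If any conditional rule is retained, reconcile the two descriptions of its trigger.

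Heteroscedasticity-robust standard errors (for example HC3) are an acceptable option but not required; they cost about 1–3 power points. The change takes one paragraph and no new data. The Trial status section reports recruitment still open at submission, so it could be made before unblinding.

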## Discussion

VO_2max_ is considered one of the most important predictors of CVD mortality; in addition to smoking, high blood pressure (hypertension) and cholesterol disorders, low CRF levels increase the risk of CVD, is associated with morbidity and mortality from the same cause, as well as with all-cause mortality [4–6, 54–58]. Epidemiological evidence shows the link between VO_2max_ and its association with chronic conditions that trigger CVD, and subsequently increase the likelihood of death [56]. Similarly, high blood pressure is associated with increased risk of CVD [21]. Therefore, finding ways to increase VO_2max_ and reduce SBP and DBP it is of vital importance to public health. Recently the cardiorespiratory improvements obtained with HIIT have been examined; however, the optimal dose necessary requires further inquiry [20]; thus, it is important to develop RCT's as the one proposed in this study, which will clarify and provide insight to the cause-effect relationship between HIIT and VO_2max_, as well as HIIT and SBP-DBP. This research is novel since it is the first to examine a HIIT workout with a heavy load with a total length 7.5 minutes per session, compared with other studies using longer load periods [11, 13, 14, 38, 39]. This project is of utmost importance, as exercise adherence is typically hindered by the lack needed to complete a typically traditionally design exercise program [28]. Another strength of this study is the design used (RCT), which has the power to detect differences in the effect on VO_2max_ produced by a HIIT vs MICT program.

## Trial status

The call for participants started on April 25, 2015. We have enrolled 29 volunteers as of the submission of this manuscript. Of those 29, 18 have finished the interventions, and two withdrew from the study for personal reasons. The remaining volunteers are active. Recruitment of all volunteers is expected to finish in June 2016.

## Abbreviations

ANCOVA, analysis of covariance; CONSORT, Consolidated Standards of Reporting Trials; VO_2max_, maximal oxygen uptake.
